#### Sample size and statistical analyses

On the basis of a study on the efficacy of an earlier study in which the investigators tested the VR system in children with cerebral palsy [29], a power analysis and sample size calculation for the present study were performed with G*Power software version 3.1.5 [30]. In the cited study of children, the BBT (primary outcome measure) showed an effect size (Cohen’s *d*) of 0.98. Assuming a similar effect size for adult stroke patients, we would need (two-tailed test, power = 0.9, significance level *P*-value = 0.05) a total of 46 patients (23 per group). Assuming a dropout rate of 20%, we will recruit a total of 60 patients across the participating centres.

Data will be analysed qualitatively and quantitatively for each patient separately. Changes will be provided as a total number or percentage. Group comparisons between EG and CG will be analysed using analysis of covariance after assessment of normal distribution. We intend to perform an intention-to-treat analyses. If necessary, an additional per protocol analysis will be carried out. Furthermore, subgroup analyses will be performed to investigate any possible study site effects. Patients’ training settings (nominal and interval data) will be analysed with frequencies and percentages to describe therapy content and provide recommendations for further therapy settings.

All study personnel will try to avoid patient dropouts. However, patients can leave the study at any time without reason. Collected patient data until the point of dropout will be included in the final analysis. Missing data will be replaced using two different approaches: (1) with the last available value carried forward method and (2) by adding or subtracting the mean difference of other patients in the respective group. Analysis with both approaches will be performed.

### Part 2

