### Part 1: randomised controlled trial

#### Study design and measurement events

The first part is designed as a randomised, controlled, assessor-blinded, multicentre trial with two parallel groups and repeated measurement events (MEs). Patients will be evaluated by a blinded assessor on five occasions: twice within 2 weeks at baseline, before intervention start (BL, T0); once after eight treatment sessions (T1); once immediately after the intervention (T2); and once after a 2-month follow-up period (FU).

*Aim*: The aim in the first part is to implement a multicentre, single-blind, randomised controlled trial to investigate the efficacy of VR training compared to conventional therapy. The first part will be implemented at three research sites in the German-speaking part of Switzerland and has two study arms: an experimental group (EG, VR training) and a control group (CG, conventional therapy).

*Research question*: The first part is designed to test the hypothesis that patients after stroke in EG show higher postintervention performance on the Box and Block Test (BBT) compared to CG patients.

*Hypothesis*: It is hypothesised (H_0_) that there will be no group differences after 16 training sessions or after the FU period. It is also hypothesised (H_1_) that there will be a group difference after the 16 training sessions and after the FU period.

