#### Randomisation and group allocation

After the patient has received written and oral study information, written informed consent will be obtained from each patient. The procedure will be performed by the clinics’ local study coordinator or the blinded assessors before patient inclusion. Documents (patient information and consent forms) can be obtained from the first author. Patients will be randomly allocated to either the EG or the CG after the second ME (T0). Group allocation will be based on a computer-generated randomisation list (one for all centres), (MATLAB release 2007b; MathWorks, Natick, MA, USA) created by a researcher not involved in the study. The randomisation list will be stored at one clinic’s pharmacy. After the second ME (T0), the treating therapist will contact the pharmacist to disclose the group allocation and the current patient will start with the respective therapy. Group allocation will remain concealed from the independent assessor until study finalisation. Patients and treating therapists will be reminded not to talk with other therapists or participants about group allocations.

As the study is single-blind, the treating therapist will be informed about the patients group allocation. If any unexpected events (severe or nonsevere) occur, the treating therapist will inform the physician on duty and the responsible study organisation personnel to initiate all necessary procedures.

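### Two pre-randomisation Box and Block scores and three sites are available, but the article gives the first score no stated role in the group comparison and handles site only through low-powered subgroup analyses

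*Protocol article*

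**What the plan says.** All references are to Part 1 of the protocol article.

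- **Measurement.** Under *Study design and measurement events*, the blinded assessor sees patients "twice within 2 weeks at baseline, before intervention start (BL, T0"), then at T1, T2 and follow-up. Table 3 lists the BBT at all five occasions.
- **Randomisation.** It takes place after T0, so both BL and T0 precede allocation. "Group allocation will be based on a computer-generated randomisation list (one for all centres"). No stratification by site is described. The Discussion presents the single list as a deliberate choice.
- **Primary outcome.** It is the BBT change from T0 to T2 (*Primary outcome: hand dexterity*). BL is not mentioned there.
- **Analysis.** "Group comparisons between EG and CG will be analysed using analysis of covariance after assessment of normal distribution". No covariate is listed. On site, the section says only that "subgroup analyses will be performed to investigate any possible study site effects".
- **Sites.** There are three, and they differ in kind: the outpatient centre of a community hospital, an academic hospital and a rehabilitation clinic (*Methods and design*).

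**The concern.** In a trial of 60 patients, a second pre-randomisation measurement of the primary outcome is worth using. Averaging two baselines removes part of the measurement error from the covariate, so the ANCOVA explains more of the variation at T2. The article collects this value and then assigns it no part in the comparison.

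Site raises a similar issue. With one list and no described stratification, the arms can be unequal within a site by chance, and the three sites may well differ in case mix. A site term in the primary model would deal with both. The article instead sends site to subgroup analyses. These leave the primary estimate as it was, and with about 20 patients per site they are too small to show whether the effect differs between sites. The stake is a wider confidence interval than necessary, and three noisy site results that could be read as real site differences.

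**Working it through.** **1. The plan's own figure.** Inputs from *Sample size and statistical analyses*: "two-tailed test, power = 0.9, significance level *P*-value = 0.05"; "the BBT (primary outcome measure) showed an effect size (Cohen’s *d*) of 0.98"; "a total of 46 patients (23 per group"). A two-sample t-test with the noncentral t distribution gives 23 per group (power 0.9015; 22 per group gives 0.888), so 46 reproduces. With 20% dropout, 46/0.8 = 57.5, rounded up to 58. The planned 60 leaves 60 × 0.8 = 48 evaluable, 24 per group, with power 0.914. The calculation takes no credit for covariates, so nothing below changes the required number.

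**2. Power within one site.** Equal sites are an assumption: 60/3 = 20 patients, 10 per arm, or 8 per arm after 20% dropout. Two-sample t-test, two-sided 0.05:

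| Effect (d) | 10 per arm | 8 per arm |
|---|---|---|
| 0.98 (planning value) | 0.55 | 0.45 |
| 0.53 (meta-analysis in the Background) | 0.20 | 0.17 |

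**3. Power of a treatment-by-site interaction.** F-test on 2 and N − 6 degrees of freedom, noncentrality (n/2) × Σ(dᵢ − mean d)², with n per arm per site. The effect patterns are assumed:

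| Site effects (d) | 8 per arm | 10 per arm |
|---|---|---|
| 0.98 / 0.98 / 0 | 0.26 | 0.32 |
| 1.47 / 0.98 / 0.49 | 0.21 | 0.25 |
| 1.96 / 0.98 / 0 | 0.67 | 0.78 |

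The interaction also has low power unless the sites differ greatly. Its advantage is that it answers the right question once, with an interval.

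**4. Gain from adding BL.** The article gives no correlations or standard deviations, so two sets of assumptions are shown.

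*(a) Equal correlation ρ between all occasions.* Residual variance, as a share of the T2 variance, is 1 − ρ² with T0 alone and 1 − 2ρ²/(1 + ρ) with the mean of BL and T0.

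| ρ | T0 alone | Mean of BL and T0 | Ratio |
|---|---|---|---|
| 0.5 | 0.750 | 0.667 | 0.89 |
| 0.7 | 0.510 | 0.424 | 0.83 |
| 0.8 | 0.360 | 0.289 | 0.80 |
| 0.9 | 0.190 | 0.147 | 0.78 |

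The reduction is 11% to 22%.

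*(b) Measurement error plus true change.* The article puts the smallest real difference at five or six cubes. If that is a 95% limit for a difference of two measurements, the error SD is 5.5/(1.96 × √2) = 1.98 and its variance e is 3.94. Take a between-patient SD of 15 (variance B = 225) and a true-change SD of s. Residual variance is s² + e + B·e/(B + e) with T0 alone. With the mean of BL and T0, e is replaced by e/2 in the last term.

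| s | T0 alone | Mean of BL and T0 | Reduction |
|---|---|---|---|
| 2 | 11.8 | 9.9 | 16.2% |
| 5 | 32.8 | 30.9 | 5.8% |
| 10 | 107.8 | 105.9 | 1.8% |

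A between-patient SD of 10 gives 15.8% and 5.7% in the first two rows.

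Across (a) and (b) the saving is about 2% to 22% of residual variance. The standard error is multiplied by √0.98 = 0.99 at one end and √0.78 = 0.88 at the other.

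**5. Gain from adding site.** This depends on the share of residual variance that site explains, which the article does not give. With 24 per group and effective d = 0.98/√(1 − share), power is 0.914, 0.926, 0.939 and 0.960 for shares of 0, 5, 10 and 20%. The degrees of freedom used by the site term are not deducted.

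**The case against.** The strongest objection is that the article names no covariate and therefore excludes none. ANCOVA presupposes at least one, and the list may stand in a full protocol or analysis plan that is not shown. That is correct. A reader might infer that the primary ANCOVA leaves out both BL and site, but the text does not say so. It shows only that neither has a stated role in the comparison, and that the one stated use of site is subgroup analysis.

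It is also fair to say that taking the last pre-randomisation value as reference is standard, and that leaving out BL or site causes no bias in a randomised comparison. Only precision is at stake. The size of the gain rests on assumptions, and it nearly vanishes if patients differ widely in their true change.

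On site, the wording does not commit the trial to three separate significance tests, so an interaction could be meant. Whichever is meant, the primary estimate stays unadjusted unless site is in the primary model. The interaction recommended here has low power too, and must be labelled accordingly.

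Two further readings are tempting and are not supported:

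- The sentence "Changes will be provided as a total number or percentage" might suggest that the primary test could use percentage change, which would be erratic when entry requires only 1 block. That sentence follows one about analysing each patient separately and is not tied to the ANCOVA. The article describes the BBT's smallest real difference in cubes.
- The reference to assessing normality might suggest that the method depends on a preliminary test. The article does not say what is assessed or what would follow from it.

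**Conclusion.** The point stands as a matter of efficiency and clear specification. It is not an error that biases the result. The article collects two valid baseline values of the primary outcome and gives only T0 a role. It handles three unlike sites by subgroup analyses that do not adjust the treatment estimate and that have power of about 0.45 to 0.55 per site at d = 0.98, less at smaller effects. The power figures assume equal sites.

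Using BL would save roughly 2% to 22% of residual variance. The upper end needs a high correlation that is equal across all occasions. The lower end applies when true change varies widely between patients. The gain from site cannot be sized from the article. The planned 46 evaluable and 60 recruited patients need no revision.

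**What to change.** State the primary model before unblinding: ANCOVA of BBT at T2, in blocks, on treatment, with the mean of the BL and T0 BBT (or both values) and site as a fixed three-level factor. With T0 among the covariates, the treatment effect is the same whether T2 or the change from T0 is the response, so the both-values version fits the primary outcome as defined.

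Replace the site subgroup analyses with one treatment-by-site interaction estimate and its 95% CI, labelled exploratory because of its low power.

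The cost is wording plus a few degrees of freedom. Site takes two, and the baseline takes one (mean) or two (both values), so four at most out of about 48 evaluable patients. No new data or patients are needed. If a full protocol or analysis plan already contains this model, it is enough to confirm that and to align the description of the site analyses with it.

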#### Primary outcome: hand dexterity

Change in hand dexterity between T0 and T2 is the primary outcome of interest. It will be measured with the BBT, which was described by Mathiowetz *et al*. in 1985 [12]. The test is easy to administer and can be quickly performed. It has been used in patients after stroke in patients with multiple sclerosis and traumatic brain injury [13]. Patients will be asked to grasp small wooden cubes and move them from one side of the box to the other as fast as possible within 60 seconds. The BBT is a reliable and valid assessment tool and provides normative data for healthy individuals in age groups ranging from 20 years to older than 75. A change of five or six cubes before and after an intervention seems to be the smallest real difference [14].

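### Missing BBT values are filled by two unranked single-imputation rules; at 20% missing T2 scores, the arm-mean-change rule raises the type I error from 5% to about 8–12%.

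*Protocol article*

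**What the plan says.** All of the relevant text is in the Protocol article, Part 1.

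- **Endpoint** (Primary outcome: hand dexterity): "Change in hand dexterity between T0 and T2 is the primary outcome of interest", measured by the BBT.
- **Analysis** (Sample size and statistical analyses): EG and CG are compared by analysis of covariance, with an intention-to-treat analysis intended.
- **Missing data** (same section): values are replaced (1) "with the last available value carried forward method" and (2) "by adding or subtracting the mean difference of other patients in the respective group". Then: "Analysis with both approaches will be performed". Neither is called primary or sensitivity, and nothing is said about what follows if they disagree.
- **Size** (same section): "two-tailed test, power = 0.9, significance level" 0.05, with Cohen's d = 0.98 taken from a study in children, giving 23 evaluable patients per group. "Assuming a dropout rate of 20%, we will recruit a total of 60 patients across the participating centres".
- **Leavers** (text under Table 3): patients who leave are still invited to every planned measurement event. Table 3 schedules the BBT at BL, T0, T1, T2 and FU.

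**The concern.** The second rule gives each missing patient exactly the average change of the others in that arm. The arm's mean change does not move, but the analysis now believes it has more patients, and the added ones lie on the mean. Spread is understated and the sample size overstated, so the reported standard error and p-value are too small. This happens even under the most benign mechanism, dropout completely at random.

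The first rule has a different weakness. It freezes a leaver at an earlier score. If scores move between visits, a treatment effect is diluted. If the arms also differ in how many leave or when, a difference can appear that treatment did not cause. Patients and therapists know the allocation, so unequal dropout is possible.

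At stake is the primary BBT test: one of the two planned analyses does not hold its 5% level once an appreciable share of T2 values is missing, and the text does not say which analysis the conclusion rests on.

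**Working it through.** **Inputs from the protocol article.** Two-sided alpha 0.05, power 0.90, d = 0.98, 23 evaluable per group, 60 recruited, 20% dropout, ANCOVA, endpoint T0 to T2. Sixty patients at 1:1 is 30 per arm; 20% missing is 6 per arm, leaving 24.

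**Assumptions, not in the document.** Rule 2 means last available value plus the mean change of the same arm's observed patients from that visit to T2. Dropout is completely at random and data are normal. The T0–T2 correlation of the BBT is not given; 0.5 to 0.95 was examined.

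**Step 1: reproduce the plan's figure.** For a two-sample t-test with d = 0.98 (noncentral t), power is 0.888 at 22 per group and 0.901 at 23, so 46 in total is right. Allowing for dropout, 46 / 0.8 = 57.5, or 58. The planned 60 leaves 60 × 0.8 = 48 completers, with power 0.914 at 24 per group. The sample size is not at fault, and it does not need filled values to reach 90% power.

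**Step 2: rule 2, closed form (last value is T0, change score).** Filled changes equal the arm mean, so the sum of squares SS is unchanged.

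- Valid variance of the arm mean: SS / (23 × 24).
- Variance that the filled analysis reports: SS / (29 × 30).
- SE ratio: sqrt[(24/30) × (23/29)] = sqrt(552/870) = 0.797.
- The critical value on 58 df is 2.002, so the filled test rejects when the valid t statistic (46 df) exceeds 0.797 × 2.002 = 1.594.
- Actual type I error: 2 × P(t46 > 1.594) = **0.118**.

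The same formula with 3 of 30 missing gives a ratio of 0.898 and a type I error of 0.078.

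**Step 3: rule 2 by simulation.** ANCOVA of T2 on T0 and group, no true difference, 30 per arm, 20,000 trials per setting:

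| Missing at T2, per arm | Last value of leavers | Type I error, rule 2 |
|---|---|---|
| 6 of 30 (20%) | T0 for all | about 0.11–0.12 |
| 6 of 30 | T1 for half | about 0.093–0.099 |
| 6 of 30 | T1 for all | about 0.077–0.083 |
| 3 of 30 (10%) | T0 for all | about 0.08 |
| 3 of 30 | T1 for all | about 0.06 |
| 1 of 30 (3%) | T0 for all | about 0.057 |

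A separate simulation gave 12.1%, 10.7% and 7.9% for the first three rows. The assumed correlation hardly matters. ANCOVA on observed T2 values alone stays at 0.046–0.053.

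**Step 4: rule 1.** With equal dropout the simulated type I error was 0.012–0.052: no inflation, and conservative when scores improve over time. If T0 is carried forward for 20% of each arm, those patients contribute zero change, so a true 5-block effect becomes 0.8 × 5 = 4.0 blocks. With 30% against 10% dropout (an assumed split) and the same mean improvement m in both arms, the apparent difference is 0.7m − 0.9m = −0.2m, which is 1 block against the arm with more dropout when m = 5.

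**Step 5: can the two rules disagree?** Illustration with a change SD of 6 blocks (assumed), 20% missing per arm, T0 as last value, and an EG advantage of 5 blocks: the two analyses disagree on significance in about 19% of trials if CG itself improves by 5 blocks, and in about 11% if CG does not improve.

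**The case against.** Several points on the other side stand.

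- **Timing of dropout.** The 12% figure requires that no leaver has a value after T0. The BBT is repeated at T1 and data up to dropout are used, so 8 to 12% is the fair range at 20% missing. A reader might take 12% as the trial's error rate; the document does not support that.
- **Dropout is not the same as a missing T2.** The 20% is a recruitment allowance, leavers are invited to all visits, and T2 falls at the end of a 4-week programme. Fewer T2 values may be missing. But an invitation does not ensure attendance, and the excess shrinks without vanishing: about 5.7% at 3% missing.
- **Wording of rule 2.** The visit from which the mean difference is taken, and the starting value, are not stated. The reading used here is the natural one, and both T0 and T1 as starting point were examined.
- **Two primary p-values.** A reader might infer these from the text. It says only that both analyses are run; it does not call either primary or give them equal standing, and an analysis plan not shown may rank them. What the article does fix is the filling rule itself, whose standard error is wrong however it is ranked.
- **Bias of last value carried forward.** One might infer that it will create a false difference here. That needs unequal dropout and scores that change over time. The document states neither, and the 30% versus 10% split is only an illustration.

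Running two methods might also be defended as an informal robustness check. That is weak: neither rule carries the uncertainty of the filled values, so agreement between them would not validate either.

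**Conclusion.** The concern holds in a bounded form. The article commits to a deterministic fill by arm-mean change which, counted as observed data, makes the standard error too small: by about 20% when 6 of 30 per arm are filled from T0. At 20% missing T2 values the two-sided type I error is about 8%, 10% or 12% when all, half or none of the leavers have a T1 value. At 10% missing it is about 6 to 8%, and with few missing T2 values it is close to nominal. These figures assume dropout completely at random, equal in both arms, and the reading of rule 2 given above.

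The inflation belongs to rule 2 alone. Last value carried forward attenuates a true effect (5 to 4 blocks if T0 is carried for 20%), and is biased only if dropout differs by arm and scores change. The lack of ranking matters because the two rules err in different ways and can disagree. The sample size reproduces and is not part of the problem.

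**What to change.** Name one primary analysis of the T0–T2 BBT comparison that does not treat filled values as observed. Either of these would do:

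- a likelihood-based repeated-measures model on all observed post-randomisation BBT values, with pre-randomisation BBT as covariate and the EG–CG contrast at T2; or
- multiple imputation by arm using BL, T0 and T1, followed by the planned ANCOVA.

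The planned ANCOVA on observed T2 values also holds about 5% when data are missing completely at random, and 48 completers give power of about 0.91 at d = 0.98. The two options above make better use of T1 from patients without a T2 value.

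Drop the arm-mean-change rule, or keep it and last value carried forward only as labelled sensitivity analyses that cannot change the primary conclusion. If the arm-mean rule is kept, state the visits between which the difference is taken and the value to which it is added.

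The cost is a few sentences of analysis text, settled before unblinding, and no new data. Confidence intervals will be slightly wider than the arm-mean rule would report.

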#### Study design and measurement events

It is highly relevant to consider the patients’ and therapists’ perspectives, in particular if new therapy systems will be evaluated regarding their effectiveness. Part 2 comprises two qualitative investigations to explore patients’ and therapists’ experiences with the VR training system. The gained knowledge can be used to improve the training system and to formulate treatment guidelines.

*Aim*: The aim of the investigations is the exploration and description of the patients’ and treating therapists’ experiences and expectations during the intervention with the VR training system. Semistructured interviews will be conducted with patients in EG and focus groups will be performed with therapists, who have trained patients with the VR training system.

*Main research question*: How do patients and therapists experience the intervention with the VR training system?

